## Abstract

**Background:**

Medication safety is an important health issue for nursing home residents (NHR). They usually experience polypharmacy and often take potentially inappropriate medications (PIM) and antipsychotics. This, coupled with a frail health state, makes NHR particularly vulnerable to adverse drug events (ADE). The value of systematic medication reviews and interprofessional co-operation for improving medication quality in NHR has been recognized. Yet the evidence of a positive effect on NHR’ health and wellbeing is inconclusive at this stage. This study investigates the effects of pharmacists’ medication reviews linked with measures to strengthen interprofessional co-operation on NHR’ medication quality, health status and health care use.

**Methods:**

Pragmatic cluster randomised controlled trial in nursing homes in four regions of Germany. A total of 760 NHR will be recruited. Inclusion: NHR aged 65 years and over with an estimated life expectancy of at least six months. Intervention with four elements: i) introduction of a pharmacist’s medication review combined with a communication pathway to the prescribing general practitioners (GPs) and nursing home staff, ii) facilitation of change in the interprofessional cooperation, iii) educational training and iv) a “toolbox” to facilitate implementation in daily practice. Analysis: primary outcome - proportion of residents receiving PIM and ≥ 2 antipsychotics at six months follow-up. Secondary outcomes - cognitive function, falls, quality of life, medical emergency contacts, hospital admissions, and health care costs.

**Discussion:**

The trial assesses the effects of a structured interprofessional medication management for NHR in Germany. It follows the participatory action research approach and closely involves the three professional groups (nursing staff, GPs, pharmacists) engaged in the medication management. A handbook based on the experiences of the trial in nursing homes will be produced for a rollout into routine practice in Germany.

**Trial registration:**

Registered in the German register of clinical studies (DRKS, study ID DRKS00013588, primary register) and in the WHO International Clinical Trials Registry Platform (secondary register), both on 25th January 2018.

## Background

The medication management of nursing home residents (NHR) is complex and can be challenging for all involved professions [1]. In Germany, doctors prescribe, community pharmacists dispense and nurses administer drugs to NHR. Due to the continuous contact with the NHR, nurses are in the best position to observe their health state. They may, however, lack knowledge about geriatric pharmacotherapy and thus cannot decide which of the changes observed in health status might be associated with drug therapy. In Germany, only doctors are authorised to prescribe, but often they do not have enough time for thorough medication reviews. On the other hand, pharmacists have in-depth knowledge on medications’ effects and interactions, however, reviewing medications is generally not part of their task portfolio and is not remunerated. Hence cooperation of the three professions is a promising approach for a safe and efficient medication management [2]. Systematic procedures on how to co-operate are not in place [3], and the professional groups involved in medication management (GPs, nursing staff and pharmacists) have been shown to poorly communicate and undervalue each other’s competencies on this matter [4].

There are strong arguments in favour of a careful medication management for NHR. Firstly, NHR are commonly exposed to polypharmacy. In a study of 21 German nursing homes, 70% of NHR received 5 or more prescribed medications [5]. Polypharmacy increases the risk of drug-interactions, and adverse drug events (ADE) such as falls [6]. Secondly, the majority of NHR has a frail health state and/or suffers from dementia. Frailty poses an additional risk of experiencing ADE resulting in earlier incident disability and mortality [7] . Thirdly, a great number of NHR are exposed to potentially inappropriate medications (PIM) [8]. Studies have reported that approximately 40% of residents receive PIM [9, 10] compared to 20–25% of patients living in the community [10]. Indeed, 20% of NHR take medication that is contraindicated or incorrectly dosed for their level of renal function [11]. Another safety issue is the administration of antipsychotic drugs [8, 12, 13]. Studies from Germany and Austria indicate that more than half of all NHR receive such drugs, the necessity of which is often proposed by nursing home staff [14].The inherent risks are over-sedation, falls, fractures [15], arrhythmias, cerebrovascular events and even premature deaths [12, 16]. These factors together present a comprehensive risk that has been associated with a clustering of adverse drug events and premature deaths for NHR [12].

Internationally, studies relating to optimising medication management in nursing homes are increasingly available. They are designed using different interventions such as pharmacist led medication reviews, improved interprofessional collaboration, training of staff or providing IT-support for medication reviews. Often these studies apply a mixture of strategies. Yet the emphasis most often lies on the pharmacist review. Several systematic reviews have attempted to pool the heterogeneous findings on the prescribing quality and NHR’ health [17–19]. The most comprehensive review by Alldred et al. includes 12 studies [19]. The investigators conclude that no firm conclusions on the effects can be drawn. However, there is an indication that medication management interventions may lead to a better quality of prescribing whereas little evidence can be found so far on health improvements [19]. Other recent reviews do not focus on nursing homes [20] or not solely aim to optimising medication for NHR [21].

In Germany, interventional studies (AMTS Ampel I and II) [2, 22] report a decrease in avoidable ADE using a multicomponent intervention including pharmacists’ advice. Yet to our knowledge a randomised trial aiming to optimise the medication management for NHR has not been undertaken.

The HIOPP-3-iTBX study stands for “General Practitioners’ Initiative to optimise Medication safety for Nursing Home Residents” – using an “interprofessional toolbox” with focus on “three main stakeholders” namely GPs, nursing staff and pharmacists. The intervention involves a pharmacist led medication review, training of all professional groups and support in a change management process using participatory action research (PAR). PAR actively involves the main stakeholders in the change and strengthens the awareness of interactions between them. The method also strengthens self-emerging context-specific solutions in nursing homes [23].

The aim of the transregional cluster randomised study is to investigate the effect of a multicomponent medication safety intervention on the prescribing quality and NHR’ health. The primary outcome is the rate of NHR receiving potentially inappropriate medications (PIM) and/or ≥ 2 antipsychotic drugs; the secondary outcomes relate to the number of falls, emergency medical contacts, hospitalisation, health costs and quality of life and cognition of NHR. We hypothesise that our interprofessional intervention will lead to an improved and more efficient medication management and to a sustainable optimisation of the medication process involving nurses, GPs and pharmacists.

## Methods

### Design and setting of the study

The multicentre cluster randomised controlled trial (cRCT) is conducted in four geographical regions in Germany (Hannover, Rostock, Düsseldorf and Tübingen), of which two have a wide rural periphery and two are more urban based. Clustering takes place at the level of nursing homes. Together, the four study centres will include a total of 760 NHR at baseline (Fig. 1).

**Fig. 1 Fig1:**
[figure not shown]
Flow chart with an overview of study steps

### Participants and materials

Study participants are NHR who are at least 65 years of age and living in long-term residential care facilities. Exclusion criteria are having a life expectancy of less than 6 months based on nurses’ judgement. In case of doubt or when a nurse’s judgement is not available, the NHR’ GPs are asked for their judgement. The eligibility criteria for nursing homes, doctors and pharmacists are described in Table 1.

**Table 1 Tab1:** Inclusion and exclusion criteria

	Inclusion criteria	Exclusion criteria
Nursing home	Size at least 30 residents, and nursing home status in accordance with German statutory social law.	Specialised nursing homes (nursing homes for ventilated patients, psychiatric homes, homes for alcohol or drug addicted patients)
Pharmacist	Serving a nursing home participating in the study, willing to be trained in performing the medication review if randomised to the intervention group.	Pharmacists who serve intervention and control group nursing homes at the same time
GP	Serving a nursing home participating in the study, willing to provide participants’ health data (current diagnoses, laboratory parameters), willing to participate in a special training if randomised to the intervention group	Currently participating in other ongoing activities about medication of nursing home residents, GPs who concurrently serve NHR in intervention and control homes
NHR	At least 65 years old and in long-term residential care	Residents with a life expectancy less than six months based on nurses’ judgement and, in case of doubt, additionally based on the GPs’ judgement, patients in vigilant coma

### Recruitment strategy

The recruitment procedure is standardised and follows several steps. First, all nursing homes covering the four areas are informed about the study by mail (September 2017). Nursing homes expressing an interest are contacted by phone or personal visit in order to describe the study in more detail, to assess whether eligibility criteria are met and whether the institution is willing to participate (see Table 1).

In a second stage, the pharmacists supplying the nursing homes and all GPs responsible for the residents of the selected nursing homes are approached by mail or fax followed by a phone call in case of a non-response (November 2017 to February 2018). One pharmacy usually supplies one nursing home. By contrast, typically several GPs share the care of NHR in one facility so that several GPs might participate per nursing home residency. If both, consent and eligibility criteria are met for pharmacists and GPs, recruitment of that nursing home can proceed to the third stage.

In the third and final step, NHR cared for by a participating GP are recruited. For ethical and data protection reasons, the nursing home staff initially approaches their residents with information about the study. If the NHR consents to be contacted by our study personnel, they receive detailed written and verbal information and clarification of any queries. If a resident has a custodian, this person is contacted by the study personnel or by the nursing home manager. For the custodians we use an adapted version of the study information and the consent form. In case of custodianship, both resident and custodian have to give their written consent or else the resident cannot be recruited. In cases where only one party gives written consent, a participation in the study is not possible. An exception are cases where residents cannot give written consent, e.g. due to cognitive or physical impairment, in which the sole written consent of the custodian is sufficient.

The consent form includes two parts: i) consent to the potential intervention and the sharing of the necessary personal and medical data and ii) consent to the cognitive assessment Mini-Mental State Examination (MMSE) [24]. It is possible to participate in the study without performing the MMSE but not without performing part i). After written informed consent has been obtained, study nurses input baseline data such as current diagnoses, laboratory parameters (obtained from the GPs) and symptoms as well as medication prescriptions into a trial database (SecuTrial®). Pharmacists can commence the medication review once the study nurse tells them that all necessary data is complete and they have received log-in data for secuTrial®.

### Intervention

Following baseline assessment (t0), the intervention will be conducted and its effects measured at 6 months follow-up (t1) (Fig. 1). The intervention consists of four elements.

Firstly, the community pharmacists in charge of the nursing homes receive a special two-day training (ATHINA = Arzneimitteltherapiesicherheit in Apotheken i.e. medication therapy safety in pharmacies) [25] in performing an IT-based medication review and a further one-day training in geriatric pharmacotherapy especially designed for the study (HIOPP-3 training) based on programmes developed for previous studies (AMTS AMPEL I and II; [2, 22]). After the completion of baseline documentation by study nurses the pharmacists perform a structured medication review. Pharmacists are trained to consider 13 potential medication problems for their medication review:no indication for a certain drug based on available diagnosesnegative benefit-risk profile (according to pharmacist’s judgement)potential relevant drug interactionpotential relevant drug-disease interactionduplicate prescriptionPIM in elderly (PRISCUS list) [26]potentially relevant side effectsapplication/usage inappropriatepossible underdosingpossible overdosingcontraindicationassess duration of treatmentother reasons

The results and advice will be documented in secuTrial® and transferred to a special fax template (“medication check fax”), to be sent to the responsible GPs. The GPs in turn assess the pharmacists’ suggestions and amend their medication prescriptions, if they deem the suggested changes appropriate. Additional prescribing specialist doctors (e.g. psychiatrist) may also be informed of medication changes, either via the GP or the nursing home.

Secondly, change management principles are introduced to enhance the involved professions’ understanding of roles and interprofessional communication as a vital part of the medication management [27]. Change management support is provided by means of three workshops which are conducted in the nursing home and to which all participating professional groups are invited. The first workshop is held around the time of baseline data collection. Trained study personnel and project managers inform the attendees about the study and its goals. They facilitate a strength and weaknesses analysis of the current medication management structures and processes. Input from all attendees is noted on cue cards. Following a discussion, specific goals for each nursing home are set and suitable tools and processes to facilitate the change process (see below in Table 2) are introduced to support communication and collaboration. Finally, an intervention handbook describing all elements of the intervention/tool box is handed out.

**Table 2 Tab2:** Toolbox content

Name	Function
Thematic map for drug safety (German name: AMTS-AMPEL-Karte)	• clues for drug induced symptoms • uses a simple traffic light system:red: for high risk drugs yellow: weighty symptoms to look out for green: clues for the need of clinical monitoring • to be used by nursing staff and GPs
Additional information for the thematic map for safety in drug therapy	• easy explanations for drugs and symptoms • to be used by nursing staff
Treatment observation sheet (German name: Therapiebeobachtungsbogen)	• to be used by nursing staff • records ongoing/new symptoms in NHR • to look out for adverse drug events
Ward round tool	• to be used in common ward roundsof all 3 partaking professions • for medical and pharmacological issues of NHR
PRISCUS list [26]	• List of potentially inappropriate medications (PIM) for senior citizens • contains 83 PIM
Hospital discharge tool	• communication aid between nursing staff and GPs • used after discharge from hospital

A second change management workshop is held 2 months later. All stakeholders discuss how they have experienced the initiation of change and what further support or agreements are necessary to progress in improving their medication management. New tools can be introduced at this stage. Attendees are also asked to finalize an action plan detailing how they wish to cooperate in the following months and which tools they intend to use.

The final change management workshop is held at the end of the intervention period (after 6 months). Here the study personnel aim to get feedback on the perceived degree and success of change, on facilitators and barriers for a potential nation-wide roll-out into routine practice. Successes will be celebrated and agreements between stakeholders for a sustained local cooperation will be made.

All workshops are protocolled, and if consent is given, audio recorded for a comprehensive change analysis across different sites.

The third element of the intervention consists of educational trainings for each professional group on polypharmacy, PIM, antipsychotics and medication management in the nursing home setting. Training is offered according to the specific needs of each professional group. The pharmacists receive the most extensive training. GPs obtain an up to 2 hour training in geriatric pharmacotherapy and information on how to use the tools to improve interprofessional collaboration. The nursing staff receives two shorts educational sessions on “adverse drug events” and “antipsychotics” in NHR.

The final element of the intervention, the toolbox, supports the practical application of new competencies offering a variety of tools for daily use. Some of the tools have been developed and tested in previous studies [2, 22]. The partaking professions can choose voluntarily from the toolbox’ items. The content of the toolbox is shown in Table 2.

### Incentives

Pharmacists allocated to the intervention group as well as GPs receive a financial compensation per medication review. As part of the preparatory phase, the ATHINA training and HIOPP-3 training sessions are offered to all pharmacists allocated to the intervention group free of charge. Pharmacists allocated to the control group can receive the ATHINA training after study completion.

Furthermore, the toolbox and findings of our study will be made available to all interested nursing homes, GPs and pharmacists after study completion in the form of a “manual”.

### Outcomes

The primary endpoint is the rate of PIM and/or antipsychotic drugs, which will be calculated based on the current medication data. The secondary endpoints/parameters are number of falls, emergency medical contacts, hospitalisation, quality of life and cognition of NHR. Moreover, health services utilisation is assessed for a health economics evaluation. Data are retrieved from the NHR themselves by interview and supplemented by routine NHR documentation in the participating nursing home. An overview of all collected data and time points is given below (Table 3).

**Table 3 Tab3:**
[figure not shown]
Overview of planned assessments/data collection [24, 36–39]

### Sample size

The sample size estimation is based on the assumption that a proportion of 50% of NHR receive PIM and/or ≥ 2 antipsychotics in Germany. This estimated figure is based on studies according to which 40% of NHR receive at least one PIM [10] and 20% receive two and more antipsychotics simultaneously [28]. We assume that an overlap of PIM and ≥ 2 antipsychotic use exists in 10%. We expect a meaningful reduction in the proportion of NHR from 50 to 30% receiving PIM and/or ≥ 2 antipsychotics.

An intracluster correlation (ICC) of ρ = 0.1 is assumed and a mean number of 25 residents per nursing home is targeted. Under these assumptions and with an α = 0.05 and a power of 80% a total of 632 residents are necessary to detect the expected difference (two-sided χ^2^-test). The one-year mortality rate is conservatively estimated as 30% [29]. With a six-months-follow-up we assume a drop-out-rate of 20% (NHR’ life expectancy in months: 47 for women/26 for men) [30]. Altogether 760 patients (and 32 nursing homes) are needed.

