### Challenges

We are aware of several challenges pertaining to the conduction of the trial in the fields of recruitment, motivation of the professionals in the intervention and control groups, and drop out.

The recruitment of nursing homes is limited due to the difficulty matching interested nursing homes with responsible pharmacists and interested GPs. Once the matching has taken place, recruiting NHR is confined to only those, whose health professionals have consented. Moreover, often legal caretakers are to be involved who additionally have to consent.

We also expect difficulties in keeping nursing homes, GPs and pharmacists allocated to the control groups motivated to provide current diagnoses and laboratory parameters of their participating patients as they will not receive a compensation for this. Once community pharmacists are randomised into the control group they do not perform a medication review and might feel disappointed. We aim to overcome these obstacles by offering nursing homes, GPs and pharmacists in the control group access to intervention procedures at the end of the study.

Finally, we anticipate an extensive loss-to-follow up of the NHR due to a short life expectancy [30], or discontinuation of participating health professionals. Our sample size calculation addresses this issue allowing a drop out of 20% of NHR within the 6 months intervention phase.

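### The recruitment target of 760 leaves 608 residents after the stated 20% drop-out, not the 632 the protocol calls necessary (a minor arithmetic error; power is kept if all 32 homes are recruited)

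*Protocol article*

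**What the plan says.** All the figures are in the protocol article.

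- **Sample size, assumptions:** the control proportion is "a proportion of 50% of NHR receive PIM and/or ≥ 2 antipsychotics in Germany", expected to fall to 30%. "An intracluster correlation (ICC) of ρ = 0.1 is assumed" and "a mean number of 25 residents per nursing home is targeted". The test is a two-sided chi-square test at α = 0.05 with 80% power.
- **Sample size, result before drop-out:** "a total of 632 residents are necessary to detect the expected difference".
- **Sample size, drop-out and total:** one-year mortality is put at 30% and six-month drop-out at 20%. The section then concludes: "Altogether 760 patients (and 32 nursing homes) are needed".
- **Design and setting:** 760 is the number of residents included at baseline, so it is a recruitment figure and not an evaluable one.
- **Challenges:** heavy loss to follow-up is expected, and the reader is told: "Our sample size calculation addresses this issue allowing a drop out of 20% of NHR within the 6 months intervention phase".

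**The concern.** Three printed numbers cannot all hold: 632 needed, 20% lost, 760 recruited. If 20% are lost, 760 does not leave 632. The assurance in the Challenges section is then wrong when measured against the protocol's own requirement.

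The number of homes does not match either. At 25 recruits per home, 760 residents would need 760 / 25 = 30.4 homes, not 32. The 32 homes fit a recruitment total of 790 (790 / 25 = 31.6).

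What is at stake is whether the headline sample size delivers what the protocol says it does, and whether the stated 80% power survives. The working takes these separately because the answers differ.

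**Working it through.** **Inputs** (Sample size section): proportions 0.50 and 0.30; two-sided α = 0.05; power 80%; ICC 0.1; 25 residents per home; drop-out 20%; 760 residents; 32 homes. Equal allocation is assumed, since no ratio is stated.

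**1. Reproduce 632.** Per arm, without clustering and without continuity correction:

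n = [1.960 × √(2 × 0.4 × 0.6) + 0.842 × √(0.5 × 0.5 + 0.3 × 0.7)]² / 0.2² = 93.0

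Design effect = 1 + (25 − 1) × 0.1 = 3.4

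Total = 2 × 93 × 3.4 = 632.4

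This matches the stated 632. It is the number before drop-out, with 25 as the *analysed* cluster size.

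**2. Apply the drop-out.**

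- Needed at recruitment: 632 / (1 − 0.20) = 790, which is 30 more than 760.
- Left from 760: 760 × 0.80 = 608, which is 24 (3.8%) fewer than 632.
- Loss that 760 can absorb and still leave 632: 1 − 632/760 = 16.8%.
- Possible origin of 760: 632 × 1.2 = 758.4, close to 760. The article states no formula.

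**3. The role of 25 per home.** In step 1, 25 is the analysed size. If 25 are instead recruited and 20% lost, 20 are analysed. The design effect is then 1 + 19 × 0.1 = 2.9 and the requirement is 2 × 93 × 2.9 = 539.4 evaluable residents, not 632. Using 25 in the design effect therefore overstates the requirement by about 93 residents, more than the shortfall of 24.

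**4. Power for 608 evaluable residents.** With n_eff = (evaluable residents / 2) / design effect,

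power = Φ{[0.2 × √n_eff − 1.960 × √0.48] / √0.46}

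| Scenario (equal home sizes) | Analysed per home | Design effect | n_eff per arm | Power |
|---|---|---|---|---|
| 632 evaluable, as in step 1 | 25 | 3.4 | 92.9 | 80.0% |
| 608 evaluable, 32 homes | 19 | 2.8 | 108.6 | 85.8% |
| 632 evaluable (790 recruited), 32 homes | 19.75 | 2.875 | 109.9 | 86.2% |
| 608 evaluable, 25 recruited per home (30.4 homes) | 20 | 2.9 | 104.8 | 84.5% |
| 608 evaluable, 25 analysed per home (608/25 = 24.3 homes) | 25 | 3.4 | 89.4 | 78.4% |

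With the planned 32 homes, recruiting 760 rather than 790 costs 86.2 − 85.8 = 0.4 percentage points. Power falls below 80% only in the last row, which needs about 24 homes instead of 32.

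**The case against.** The strongest reply is that nothing is lost under the plan as written. The same sentence fixes both 760 residents and 32 homes, and that combination gives about 86% power after 20% loss, above the promised 80%. This stands, and it limits the point to a wrong stated number.

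A second reply is that 760 could rest on mortality alone. A 30% one-year mortality implies 1 − √0.7 = 16.3% at six months, and 632 / (1 − 0.163) ≈ 755, also near 760. This shows that the origin of 760 is not settled. It does not remove the conflict, because both the Sample size and the Challenges sections name 20%, not 16.3%, as the allowance. Nor does the condensed article format or an unseen analysis plan help: the conflict is between printed figures, not an omission.

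Three stronger readings are tempting, and the documents support none of them:

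- *The trial falls below 80% power.* The 78.4% figure needs 25 residents analysed per home in about 24 homes. The protocol asks for 32, and nothing in it suggests recruiting fewer, larger homes.
- *Unequal home sizes or a small-sample reference distribution make the shortfall serious.* Either could lower power, but the article gives no variation in home size, and both would affect a trial of 790 as well. They are not consequences of this slip.
- *The authors multiplied by 1.2.* That is the likelier route, but it is an inference.

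**Conclusion.** The sample size statement is wrong as written, and the error is minor. Against the protocol's own 632 and 20%, the target of 760 falls 24 evaluable residents short, the matching recruitment figure is 790, and 760 covers a 16.8% loss. The shortfall follows from the printed numbers, whichever way 760 was reached.

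The unclear use of 25 per home is a second inconsistency, and it works in the trial's favour. With 32 homes of equal size, an ICC of 0.1 and 20% loss spread evenly across homes, power is about 86%, so the stated 80% is kept. This should not be reported as a material loss of power.

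**What to change.** Restate the sample size in one of two ways:

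1. 790 residents recruited for 632 evaluable at 20% drop-out, with the total of 760 in the Abstract and in the design section changed to match; or
2. without further enrolment, 760 residents recruited in 32 homes, giving 608 evaluable at 20% drop-out (19 per home, design effect 2.8) and about 86% power under equal home sizes.

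In either case, say whether 25 per home means recruited or analysed. Correct the Challenges section so that it cites either the 608 evaluable residents with the recalculated power, or the 16.8% loss that 760 covers against 632.

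The second option costs text only and needs no extra residents or homes. That matters because the Trial status section reports recruitment already concluded in more than half of the homes. The first option raises the stated target by 30 residents but needs no more than the 32 homes already planned (790 / 25 = 31.6).
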